## Methods

### Overall Study Design

This BPA-TECH study will use mixed methods and nonrandomized controlled trial designs (ie, controlled before-after study) to implement and evaluate a BPA aimed at reducing inequities in the use of ADTs among children and adults with T1D. Phase 1 will be a qualitative mixed methods study to develop, implement, and refine the BPA. Phase 2 will be a prospective nonrandomized matched pair intervention design to evaluate the effectiveness of the BPAs in promoting prescribing and thus patient use of ADTs. The study organizing committee will be represented jointly by principal investigators in the T1DX-QI coordinating center and Johns Hopkins University, while the T1DX-QI will be responsible for the data management and analysis. We adhered to the SPIRIT (Standard Protocol Items: Recommendations for Interventional Trials) guidelines (Multimedia Appendix 1) in the development of this study protocol and all items from the World Health Organization Trial registration dataset are included [31,32]. Protocol amendments will be communicated during monthly meetings between the organizing committee and the participating clinical sites, and updates will be posted on ClinicalTrials.gov. The timeline for this 3-year study is shown in Figure 1.

**Figure 1 figure1:**
[figure not shown]
Best practice advisory development and implementation process. AID: automated insulin delivery; BPA: best practice advisory; CGM: continuous glucose monitoring.

### Study Setting

In 2016, through financial support from the Leona M. and Harry B. Helmsley Charitable Trust, T1D Exchange established the T1DX-QI, which initially included 10 diabetes and endocrinology centers focused on population health by advancing quality improvement, health equity, and real-world studies. The network has since expanded to include 62 T1D and 20 type 2 diabetes (T2D) centers, along with partners in primary care.

T1DX-QI manages more than 10 multicenter projects annually, with 4-10 centers participating per project, and has expanded its scope to include equitable access to diabetes technology and devices for both T1D and T2D populations.

In phase 1 of the study, we will recruit health care providers specializing in diabetes management from academic hospitals affiliated with the T1DX-QI. People with T1D or their caregivers will be recruited from the T1DX online registry, which includes individuals across the United States who may receive care in community clinics or academic hospitals. Phase 2 of the study will also encompass participating clinical sites affiliated with the T1DX-QI, specifically academic medical centers.

### Phase 1: Implementation

#### Stakeholder Input

During the qualitative phase of this study, we will use electronic surveys and conduct focus group sessions and structured interviews of (1) pediatric and adult endocrinology and diabetes health care providers from centers who are part of the T1DX-QI and (2) people with T1D and their caregivers. The objective of the qualitative phase of this research study is to solicit stakeholder input regarding the perceived utility, design, functionality, benefits, and potential challenges of a BPA targeting increased ADT prescribing for people with T1D. We will use the Agency for Healthcare Research and Quality (AHRQ) “Five Rights” for effective CDS [33] (Table 1) and the T1D Exchange Health Equity Framework as guiding frameworks [34].

For the health care providers, 8 focus groups will be conducted with a multidisciplinary group of providers (approximately 3 to 5 participants per focus group) selected from centers participating in the T1DX-QI collaborative to understand systems barriers to incorporating a BPA, criteria that would trigger the BPA, and reasons for deciding not to prescribe ADTs to patients. The focus group guide is provided in Multimedia Appendix 2. Eligible participants will be physicians, advanced practice providers, certified diabetes care and education specialists, and nurses who are involved in the care of patients with T1D and have expertise in the management of ADTs along with IT specialists involved in the development of BPAs. An incentive of US $150 remuneration will be provided to focus group participants. In addition, 4 questions related to the proposed BPA were sent to all participating centers in the T1DX-QI as part of their annual survey (Multimedia Appendix 3).

**Table 1 table1:** Agency for Health Care Research and Quality 5 rights of effective clinical decision support frameworks to guide electronic surveys and focus group sessions.

Five rights of clinical decision support	Provider	Patients
Right information	How to translate ADA^a^ standards of care for CGM^b^ and insulin pumps into prompt and alert? Reason device not offered or declined?	What information would be helpful to you in making a decision about using ADT^c^? Reasons device declined?
Right person	Who should receive the prompt? Endocrinologist or diabetes advanced practice provider? Primary care physician?	Who should receive the information about technology (patient only, parent, primary care physician)?
Right intervention format	Define BPA^d^ inputs	MyChart notification?
Right channel	Order entry Progress note template Level of service (closing chart) Health maintenance or care gap	MyChart notification Previsit questionnaire Postvisit questionnaire
Right timing	Previsit charting During encounter When closing encounter How often? Once, 3 months, 6 months, 12 months?	Before visit? After visit? How often? Once, 3 months, 6 months, 12 months?

^a^ADA: American Diabetes Association.

^b^CGM: continuous glucose monitoring.

^c^ADT: advanced diabetes technology.

^d^BPA: best practice advisory.

All participating intervention centers currently use the Epic EMR system; therefore, focus group sessions will also be guided by Epic’s CDS setup and support guide as a reference to inform the questions for the focus group session and qualitative interviews. It is important to note that EHR systems often use varying terminology to describe CDS alerts. For instance, the Epic EMR vendor recently renamed its “Best Practice Advisory” to “Our Practice Advisory.” To maintain consistency throughout this study, we will use the term “BPA” to refer to CDS alerts.

For people with T1D and caregivers, we will administer a 20-item Qualtrics questionnaire on the T1D Exchange Online Registry, which is accessed by approximately 19,000 caregivers or individuals with T1D who have consented to be contacted about additional studies. People with T1D or caregiver survey (Multimedia Appendix 4) will address (1) the perceived need for the BPA, (2) benefits and concerns, (3) relevant information and communication approaches, (4) the importance of person-centered care, and (5) user interface and alerts. The goal is to survey approximately 50 caregivers of youth with T1D and 50 adults with T1D. Participants completing the electronic survey will be offered the opportunity to participate in a follow-up structured interview.

We will conduct structured interviews with approximately 10 caregivers of youth with T1D and 10 adults with T1D to capture people with T1D perspectives on BPAs related to ADTs (Multimedia Appendix 5). For both the interviews and survey, we will recruit a representative sample of 50% non-Hispanic Black and Hispanic people with T1D. Participants will receive a US $100 payment for time remuneration.

All focus group sessions for both health care providers and people with T1D or their caregivers will be conducted by T1DX-QI staff trained in qualitative interviewing. Focus group sessions will be audio-recorded, transcribed, and exported into NVivo software (NVivo version 13, Lumivero) for data organization and management and will continue until thematic saturation is reached. Focus group guides may be iteratively adapted based on insights gathered during the sessions.

#### Intervention Centers

A total of 7 T1DX-QI clinical centers, consisting of pediatric and adult diabetes specialty clinics in the United States (Table 2), will participate in both the development and implementation of the BPA. A 7-item Qualtrics survey was distributed to all clinical centers within T1DX-QI to gather information on their EMR systems, capacity to develop automated alerts for CGMs and AIDs, IT capacity and commitment to the project, anticipated EMR freezes or delays during the planned intervention period, typical timeline for EMR changes at the institution, and previous experience building BPAs. Based on these responses, centers were selected to ensure geographical representation of the United States and a balance of pediatric and adult centers, with priority given to clinical centers using Epic EMR and demonstrating capacity, interest, and commitment to the project.

**Table 2 table2:** Intervention clinical centers.

Intervention center	Clinical center	Geographical region	Pediatric or adult
1	Johns Hopkins	Mid-Atlantic	Pediatric and adult
2	Hassenfeld Children’s NYU^a^	Northeast	Pediatric
3	Upstate Medical University	Northeast	Adult
4	Nationwide Children’s	Midwest	Pediatric
5	Grady Memorial	Southeast	Adult
6	University of Texas Southwestern	Southwest	Pediatric
7	Seattle Children’s Hospital	Northwest	Pediatric

^a^NYU: New York University.

Each center will have a designated principal investigator who will participate in monthly meetings with the organizing committee. Johns Hopkins University, which includes both pediatric and adult diabetes centers, will be the primary center for the development of the BPA. This center will oversee prototype development, testing, and postlive validation.

#### BPA Development

The BPA development phase of this study will encompass several stages: design, testing, training, postlive validation, deployment, and ongoing refinement (Figure 1).

##### BPA Design

Using a rule-based algorithm, the EMR-based BPA will be designed to recommend ADT prescriptions for people with T1D not already using an AID system, and this would also encompass an alert for people not using CGM (and thus not using AID). The specific functionality of the BPA will be guided by the thematic analysis of the stakeholder input obtained in phase 1. The function will generate a BPA if a patient is not using an AID system and will suggest to the provider to discuss and prescribe technologies for using an AID system.

The BPA design will be led by the study organizing committee with direct involvement and support from Epic IT analysts and developers at Johns Hopkins University. Iterative feedback will be obtained from the principal investigators at each of the participating intervention centers during the prototype development. Table 3 outlines the key considerations for the design team. Throughout the design process, Norman’s user-centered design principles will be applied to ensure the BPA is intuitive, user-friendly, and meets the needs of all stakeholders [35].

**Table 3 table3:** Key considerations for best practice advisory (BPA) design team.

Consideration	Descriptions
Stakeholder input	Incorporate thematic analysis of feedback from patients, caregivers, and health care providers.
Algorithm rules	Define criteria for triggering the BPA based on patient EMR^a^ data.
Workflow integration	Ensure BPA integrates seamlessly into the provider’s workflow.
Iterative testing	Conduct iterative testing and refinement based on feedback from pilot implementations.
Setting and restrictions	Consider the setting (ambulatory, inpatient, both) and specific locations such as endocrinology clinics, primary care clinics, or health-system wide.
Location in Epic	Determine the BPA’s location in Epic, such as Windows, BPA Navigator, or Flag in Storyboard.
Active versus passive	Decide between active (windows that appear in the user’s Epic workflow) and passive (appear within assigned locations that fit into the end user’s workflow) BPAs.
Clinician action	Specify actions clinicians can take, such as placing orders or referrals.
Triggering messages	Determine language in the BPA, including potential references to practice guidelines, explain the reason for the BPA, and suggest actions to be taken.
Iterative testing	Conduct iterative testing and refinement based on feedback from pilot implementations.

^a^EMR: electronic medical record.

##### BPA Testing

After a prototype BPA is developed, the testing phase will involve incorporating the BPA into integrated testing scripts in the Epic sandbox environment. The prototype BPA will be tested thoroughly in an environment using realistic data. A debugging tool will test specific cases in the BPA builder before actual deployment. Site principal investigators will be asked to provide direct oral or written feedback about the usability of the BPA and will be encouraged to suggest improvements.

##### BPA Training

Minimal provider training is expected as BPAs are widely used in the EMR. However, Epic tip sheets and a communication strategy will be developed by each of the intervention centers to facilitate the training process. Communication methods may include email and Microsoft Teams posts to ensure that all relevant staff are informed and prepared to use the BPA effectively.

##### Postlive Validation

Initially, the BPA will be launched at Center 1 (Johns Hopkins University) to allow for an in-depth assessment and troubleshooting of any potential issues before wider deployment. This initial launch will involve a thorough 90-day validation phase, during which the functionality and impact of the BPA will be closely monitored and evaluated. During this validation phase, any issues or inefficiencies identified will be addressed and rectified. In addition, during this period, the intervention centers will begin the process of obtaining local institutional approval for the BPA. This approach ensures that the BPA is fully optimized before it is implemented at the remaining 6 intervention centers (centers 2-7).

##### Deployment

Following the successful completion of the validation phase at Johns Hopkins University, the BPA will be rolled out sequentially to the other intervention centers. Each institution has a CDS committee that approves new builds, and this approval process will be factored into the timeline (Figure 2). Each of the participating intervention centers has already received letters of support from institutional IT leadership; therefore, we do not anticipate any approval barriers. To ensure that each intervention center is prepared to launch the BPA at the same time, the organizing committee will recommend that the approval process for the build occur at least 90 days before the planned launch. This staged deployment strategy minimizes the risk of widespread issues and allows for iterative improvements based on real-world feedback. Once the study team has ensured that the target providers at the other 6 participating centers have received requisite training, the BPA will be moved into the Epic production environment, which will correspond to the start of the intervention phase of the study.

After deployment, we will monitor adherence to the BPA using SlicerDicer, an analytics tool integrated within Epic. This tool enables us to track the frequency of BPA activations, the acknowledgment reasons selected by clinicians, and the subsequent actions taken. SlicerDicer allows for the creation of custom reports and dashboards that visualize compliance trends over time and facilitates in-depth analysis of specific instances of noncompliance. These insights will be used to generate feedback reports for clinicians, enabling clinical leaders to compare provider compliance rates against their peers and internal benchmarks. This approach aims to encourage adherence to BPAs and foster a culture of continuous quality improvement.

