### Phase 2: Evaluation (Study Design)

Using a nonrandomized matched pair-intervention design (ie, controlled before-after study), we will compare the use of ADT following the BPA intervention among non-Hispanic Black and Hispanic people with T1D at 7 participating T1DX-QI centers. These will be matched with control non-Hispanic Black and Hispanic people with T1D at nonintervention T1DX-QI centers over a 12-month period. Both control and intervention centers have completed the EMR data mapping to the T1DX-QI, allowing for consistent outcome assessment across both groups. The study will consist of 2 distinct periods:

Baseline period (before): 12 months before deployment of the BPA at the intervention centers.Implementation period (after): 12 months after the deployment of the BPA at the intervention centers.

The before-after matched-pair intervention design allows for a real-world assessment of the BPA’s impact on ADT use while controlling for key confounders. Comparing ADT prescribing before and after BPA implementation within intervention sites and using matched controls from nonintervention centers, the design also accounts for site-specific prescribing patterns and secular trends. This quasi-experimental approach is practical for an EMR-based intervention and minimizes selection bias by matching key clinical and demographic variables.

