Propensity scores will be estimated using logistic regression, where the outcome variable is the likelihood of receiving the BPA intervention. The model will include the identified patient-level and clinical center–level covariates as predictors. The estimated propensity score represents the predicted probability that a given patient would receive the BPA based on their covariate profile. Patients in the intervention group will be matched to patients in the control group using a 1:4 matching ratio. Nearest neighbor matching without replacement will be used, ensuring that each control patient is only matched once. The matching process will aim to minimize the distance between propensity scores of matched pairs, thus creating comparable groups. The quality of the matching process will be assessed by comparing the distribution of covariates between the matched intervention and control groups. Standardized mean differences will be calculated for each covariate to ensure balance, with a standardized mean difference of less than 0.1 indicating adequate balance. In addition, a visual inspection of propensity score distributions before and after matching will be conducted to confirm the success of the matching process.

To assess the robustness of the results, sensitivity analyses will be performed using different matching algorithms (eg, caliper matching and kernel matching) and varying the matching ratio (eg, 1:3). In addition, the impact of imputation on the results will be examined by comparing outcomes using datasets with and without imputed values.

For nonstatic matching variables (eg, laboratory results), the last available result in the baseline period of 12 months before the BPA deployment date in the intervention centers will be used.

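### The stated start of the intervention phase leaves at least 90 days of live advisory inside Center 1's baseline year, and the rollout wording leaves the dates for the other centers and the controls unsettled

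*Protocol article*

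**What the plan says.** Postlive Validation puts one center ahead of the rest: "Initially, the BPA will be launched at Center 1". It adds: "This initial launch will involve a thorough 90-day validation phase". Sandbox testing is described before this, under BPA Testing, so the validation takes place with the advisory in live use.

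The Deployment section says that, once validation has succeeded, "the BPA will be rolled out sequentially to the other intervention centers". A few sentences later it gives the reason for early approvals: "To ensure that each intervention center is prepared to launch the BPA at the same time". The paragraph ends by saying that, after training at the other 6 centers, "the BPA will be moved into the Epic production environment, which will correspond to the start of the intervention phase of the study".

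The analysis windows depend on this deployment. Phase 2: Evaluation (Study Design) sets the baseline at "12 months before deployment of the BPA at the intervention centers" and the implementation period at "12 months after the deployment of the BPA at the intervention centers". For time-varying matching variables, the Control Group section says that "the last available result in the baseline period of 12 months before the BPA deployment date in the intervention centers will be used", with the date in the singular. Primary Outcome ascertains baseline technology status, in both groups, over the 12 months before deployment. The Results section describes one deployment followed by one 12-month evaluation ending around July 2026. The exclusion criteria remove patients already using AID at baseline; the inclusion criteria keep those with CGM only.

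**The concern.** A controlled before-after comparison needs a baseline free of the intervention. If the clock starts when the other 6 centers go live, Center 1 has by then had the advisory for at least 90 days, and that time falls in its before period.

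The loss is selective. A Center 1 patient whom the advisory moves to AID in those days becomes a baseline AID user and leaves the analysis. One who starts CGM is recorded as a baseline CGM user and can no longer count through the No CGM to CGM transition. Controls in the same calendar period lose only their background progressors. What is lost in excess at Center 1 is therefore progression that the advisory caused, which pulls that center's estimate toward no effect.

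For centers 2-7 the question is which rollout statement governs. If they go live on different dates, a common date misdates their windows: a center launching earlier has treated time in its baseline, and one launching later has untreated time in its follow-up.

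**Working it through.** The plan gives no figure for this overlap, so there is none to reproduce. The check sets the go-live order against the windows and then sizes the result.

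**Inputs**
- Lead of Center 1: at least 90 days (Postlive Validation; rollout follows completion of validation).
- Baseline window: 12 months, taken as 365 days (Phase 2: Evaluation).
- Control progression: 15% over 12 months (Power).
- Differences considered: 15 points, and 5 points as the smallest case (Power).
- Intervention patients: 3000 across 7 centers (Results). Center 1's share is not given. Assumption: 1/7, with 10% and 30% as the range.

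**Step 1. Overlap.** 90 / 365 = 0.247, about 25% of Center 1's baseline year.

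**Step 2. Progressors in the window, with progression even over the year.**

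| Case | All progressors | Background | Due to the advisory |
|---|---|---|---|
| 5-point effect (20% v 15%) | 0.247 × 20% = 4.9% | 0.247 × 15% = 3.7% | 0.247 × 5% = 1.2% |
| 15-point effect (30% v 15%) | 0.247 × 30% = 7.4% | 3.7% | 0.247 × 15% = 3.7% |

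Only the last column differs between the groups. With Center 1 at 3000 / 7 ≈ 429 patients, it is about 429 × 1.2% ≈ 5 to 429 × 3.7% ≈ 16 patients.

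**Step 3. Effect on the overall difference.** Observed difference = (1 − share × 0.247) × true difference. This treats the advisory's gain at Center 1 as a fixed amount, of which 0.247 is used up before follow-up begins and is not made up later.

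| Center 1 share | True 5 points | True 15 points |
|---|---|---|
| 10% | 4.88 | 14.63 |
| 1/7 | 4.82 | 14.47 |
| 30% | 4.63 | 13.89 |

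**Step 4. Outer bound.** If Center 1's whole effect fell within validation, the difference would be (1 − share) × true difference. At a share of 1/7 that is 6/7 × 5 = 4.29 and 6/7 × 15 = 12.86.

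**Step 5. Scale in power.** As a yardstick, and not the plan's own calculation, a simple two-proportion comparison of 15% v 20% has 90% power with 1212 per arm. At the same size, power is about 88% for the 4.82-point difference and about 80% for the 4.29-point bound.

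**Step 6. Centers 2-7.** Each month by which a center's go-live departs from a common date misplaces 1/12 of one of its 12-month windows. No total can be given, because the text does not settle whether the launches are staggered.

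**The case against.** The strongest reply is that the overlap is a matter of reading. The Phase 2: Evaluation section refers to deployment at the intervention centers, which could be taken center by center; then no treated time falls in any baseline. The sentence about the start of the intervention phase concerns the other 6 centers and gives no window for Center 1. The remark about launching at the same time is about readiness and approvals, and a launch at Center 1 followed by the rest is itself a staged rollout. The study timeline (Figure 2) is not shown and may carry center dates.

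Part of this stands. That one section, read alone, does allow center-specific dates, and nothing is held against the missing figure. But the text never states such dates, while the Deployment, Control Group and Results sections point to one date and one evaluation year. The plan thus fixes a start that creates the overlap, which is more than a detail left to another document.

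Three stronger readings are not supported.
- A reader might infer that about 5% of Center 1's patients are lost because of the advisory. The 4.9% in Step 2 includes background progression, which controls lose too.
- A reader might infer that all early responders are excluded. Only AID starters are; new CGM users stay eligible and can still meet the endpoint through No AID to AID.
- A reader might infer that treated baseline time and misaligned controls occur together at Center 1. They belong to different readings: a common date gives controls a shared calendar window, while center-specific dates remove the overlap but leave controls without a stated index date.

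It is also fair that nothing in the text supports the bound in Step 4. Center 1 still has 12 months of live advisory in follow-up. If the advisory kept producing new progressors at an undiminished rate, the shrinkage would be smaller than in Step 3.

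**Conclusion.** The point holds in a limited form. With the start date that the Deployment section states, at least 90 of 365 days of Center 1's baseline year is exposed to the advisory, and the eligibility and outcome rules turn part of its early effect into exclusions or baseline status. The bias is toward no effect and modest: roughly 1.2% to 3.7% of Center 1's patients, and an overall 5-point difference falling to about 4.8 (15 points to about 14.5). These figures rest on a 1/7 share for Center 1, an effect spread evenly over time, and a lead of exactly 90 days; a longer lead or larger share increases them. For centers 2-7 the documents establish only that the rollout statements need reconciling and that, if launches are staggered, neither a common date nor center-specific dates are fully specified for both groups. The correction is worth making because it is cheap and because the anchor date governs eligibility, matching and the primary outcome. It should be settled before outcome data are seen.

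**What to change.** 1. Reconcile the sequential and same-time statements in the Deployment section.
2. Define baseline and 12-month follow-up for each intervention center from its own first production go-live. For Center 1 this is the first launch, so the validation period counts as follow-up. Setting those 90 days aside from both periods in the primary analysis would again discard early responders. Because the advisory may be corrected during validation, add a sensitivity analysis that excludes Center 1 or its validation period.
3. Give each matched control the go-live date of its matched patient's center, and use it for baseline technology status, matching variables and follow-up. Eligibility and covariates depend on that date, so candidates should be assessed and matched within each go-live date.
4. Cut the data only after 12 months have elapsed at every center.

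The cost is protocol wording and somewhat more date handling in the extraction. Data Collection says that outcome data arrive monthly, so no new collection is needed. A late-launching center could push the cut beyond July 2026; the Abstract's completion date of May 2027 leaves about 10 months after that.
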